### Data Collection

Baseline data were collected from participants during recruitment. Follow-up (outcome) data were collected by monthly phone calls at 1 to 6 months postdelivery. Process evaluation (evaluation survey and in-depth interviews) was undertaken at completion of the study. Quantitative data were collected on Android tablets using the Dimagi CommCare app [35] to reduce errors and facilitate data processing. All questionnaires were pretested prior to transferring to tablets. Full details of the baseline, follow-up, and process evaluation measurements and timing of each measurement are shown in Table 1.

### Baseline Data Collection

Baseline questionnaires comprised instruments which have been validated and tested for reliability and were adapted from the 2011 Myanmar Multiple Indicator Cluster Survey [4] 2015, Myanmar census questionnaires [36], the 2011 Demographic and Health Survey, Bangladesh [7], and a 2012 study from Shanghai, China [37]. At baseline, participants were asked to provide information on their socioeconomic status, previous pregnancies and breastfeeding history, knowledge and sources of breastfeeding information, confidence to breastfeed and perceived self-efficacy to breastfeed, intention to breastfeed, and intended breastfeeding patterns.

**Table 1 table1:** Summary of instruments used at various times in the M528 trial.

Instruments	Baseline	Postpartum month					
		1	2	3	4	5	6
Individual socioeconomic factors (participant and husband): age, sex, ethnicity, religion, education, occupation	x						
Household factors: income level, wealth index	x						
Previous pregnancy, childbirth and breastfeeding experience	x						
Breastfeeding knowledge level (high/medium/low)	x						
Intention and confidence to exclusively breastfeed	x						
Breastfeeding self-efficacy scores (high/low)	x	x		x		x	
Postdelivery survey: date of birth; place of birth; type of delivery; and child’s birth, weight, and sex		x					
Child morbidity characteristics: signs and symptoms of fever, cough, respiratory tract infection, diarrhea, dysentery		x		x		x	
Breastfeeding and other feeding follow-up module—24-hour recall and 1-month recall		x	x	x	x	x	x
Social desirability scale (high/medium/low)						x	
Process evaluation on mHealth (intervention group only): frequency of text messages received, user-friendliness of the messages received, perceived relevance of messages, trust in messages, understanding of messages, and new information learned or not							x

We will examine the relationship between breastfeeding duration and self-efficacy using self-report Likert scales (no confidence= 1, somewhat confident= 2, sometimes confident= 3, confident= 4, very confident= 5) [38,39]. With 5 levels of responses to 33 items, total scores range from 33 to 165 and will be categorized as low self-efficacy (1 to 82) and high self-efficacy (83 to 165).

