### Follow-Up Data Collection

Follow-up comprised a postdelivery survey, feeding follow-up assessments, morbidity, breastfeeding self-efficacy, and social desirability assessments. Questionnaires have been adopted from the Global Strategy for Infant and Young Child Feeding [6] indicators for assessing infant and young child feeding recommendations by WHO [38-40], breastfeeding efficacy scales [41,42], a short version of the Marlowe-Crowne Social Desirability Scale [43], and unpublished questionnaires being used in ongoing projects in Bangladesh (MJD and ML) and Indonesia (MJD).

The postdelivery form was completed when the child was 10 days old and was used to assess his or her postdelivery status, including the date, place, and type of delivery and the child’s birth weight, sex, and perinatal outcomes. The feeding follow-up form was completed every month and asked if the child was breastfed and if other liquids or foods were given in the last 24 hours and over the preceding month since the last contact (or birth for the first follow-up). Each participant completed 6 assessments of their feeding practices, including detailed information about the different types of liquids and foods (Textbox 1).

Child morbidity status and self-efficacy were assessed when the child was 1, 3, and 5 months of age using items from a validated instrument [7,41,42]. Child morbidity questions were used to record whether the child has had any signs or symptoms such as fever, cough, cold, running nose, rapid breathing, difficulty in breathing, chest indrawing, and diarrhea and dysentery. If one of these was present, we further explored the duration of illness. Breastfeeding self-efficacy was collected at 1, 3, and 5 months postdelivery to ascertain the mothers’ confidence to breastfeed, the relationship between self-efficacy and breastfeeding duration, and whether text messages improved breastfeeding self-efficacy. Studies report that women with a higher perceived self-efficacy for breastfeeding tend to initiate breastfeeding and persist even through challenges, and we hope that women in our study will increase their confidence or self-efficacy to continue EBF because of the knowledge gained from the text messages they received [41,42,44,45].

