### Data Analysis

Quantitative data were collected via tablets and automatically submitted to the Dimagi server from which we could monitor data and generate reports. Stata software version 13 (StataCorp LLC) was used for data analyses. The intervention and control group outcomes will be compared using intention-to-treat principles [61]. Descriptive analyses were used to summarize participant baseline characteristics and breastfeeding practices. Likert scales were analyzed using Mann-Whitney U tests or cumulative odds ratios and proportions between groups using chi-square tests. Duration of EBF was compared by survival analyses with log-rank tests for between-group comparisons. If differences in baseline characteristics of the groups are identified, multivariable analyses will be undertaken. We report results using the CONSORT guidelines for reporting of randomized trials [62]. As follow-up data collection had to rely on the mothers’ self-reporting alone, we adjusted the potential social desirability bias [43] in our analyses to confirm the accuracy of self-reported outcome measures.

For process evaluation, we used Stata software for survey data analysis. We conducted descriptive analyses to summarize participant baseline characteristics and their experiences and feedback about receiving text messages. Text message delivery success was measured by the frequencies of messages received, and proportions were compared with chi-square tests. For the qualitative study, we used thematic analysis. All digitally recorded interviews were transcribed verbatim in Burmese in Microsoft Word and were reviewed to check for accuracy and translated to English. A list of thematic codes was developed by MPH, which was independently reviewed and verified by AA. The data were then be manually coded by MPH for emerging themes, which were again verified by other investigators and the most relevant themes are summarized in a document.

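### The high/low self-efficacy bands do not fit the scale: low starts at an unattainable score of 1, and the cut at 82/83 is half the maximum, 16.5 points below the midpoint of 99, with no basis stated

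*Protocol article*

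**What the plan says.** Under Baseline Data Collection, the article sets up a self-report Likert instrument coded "no confidence= 1, somewhat confident= 2, sometimes confident= 3, confident= 4, very confident= 5". The next sentence gives its length, "With 5 levels of responses to 33 items", and then both the range and the categories: "total scores range from 33 to 165 and will be categorized as low self-efficacy (1 to 82) and high self-efficacy (83 to 165").

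Table 1 lists the measure in its two-category form, "Breastfeeding self-efficacy scores (high/low"), at baseline and at postpartum months 1, 3 and 5.

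Two uses are named. Baseline Data Collection relates self-efficacy to breastfeeding duration. Follow-Up Data Collection repeats that aim and adds the question of "whether text messages improved breastfeeding self-efficacy".

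Data Analysis takes a different line on scales of this type: "Likert scales were analyzed using Mann-Whitney U tests or cumulative odds ratios". It does not say whether this means single items, the total score or the two categories.

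Under Outcome Measures, self-efficacy is neither the primary outcome nor among the listed secondary outcomes.

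**The concern.** One sentence gives a scale with a floor of 33 and a low band that starts at 1. On its own the wrong floor is a slip in wording. It matters because the cut looks like a product of the same slip: 82/83 is where one would divide a scale running from 0 or 1 to 165. On the scale actually used, that places the boundary well below the middle, and women whose answers average less than the central response are labelled high.

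Two stated aims are at stake: whether the messages raised self-efficacy, and whether self-efficacy goes with longer breastfeeding. Dividing a score with 133 attainable values (33 to 165) into two groups loses information under any cut. It loses more when the cut falls far from the centre of the observed scores. The article also leaves unclear which form governs, since Baseline Data Collection and Table 1 specify categories while Data Analysis points to rank or ordinal methods.

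**Working it through.** **Inputs from the article (Baseline Data Collection).** 33 items; item codes 1 to 5; stated range 33 to 165; low 1 to 82; high 83 to 165.

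**1. Reproduce the stated range.** Minimum = 33 × 1 = 33. Maximum = 33 × 5 = 165. The statement "total scores range from 33 to 165" is correct.

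**2. Compare the bands with the range.** The band "low self-efficacy (1 to 82") includes 1 to 32, which no respondent can score. In practice low is 33 to 82, which is 50 attainable totals. High is 83 to 165, which is 83 attainable totals.

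**3. Locate the cut.**
- Boundary between 82 and 83: 82.5
- Half the maximum: 165/2 = 82.5
- Midpoint of a scale from 1 to 165: (1 + 165)/2 = 83
- Midpoint of the attainable range: (33 + 165)/2 = 99

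The boundary equals half the maximum, and is within half a point of the middle of a scale starting at 1. It is 99 − 82.5 = 16.5 points below the midpoint of the real scale.

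**4. Read the cut in terms of answers.** The lowest high score is 83, a mean item score of 83/33 = 2.52. It lies (83 − 33)/(165 − 33) = 50/132 = 38% of the way up the scale. Seventeen items at 3 and sixteen at 2 give 51 + 32 = 83, so a woman can be classed as high without choosing either of the top two responses on any item. The 16 totals from 83 to 98 (mean item score 2.52 to 98/33 = 2.97) lie below the midpoint and are called high.

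**5. Size, by assumption.** The article gives no mean or SD for the score. Take a normal score with SD 20 and let the mean vary; both are assumptions.
- Proportion called low: p = Φ(z), with z = (82.5 − mean)/20.
- Share of the information in the continuous score that a split keeps: φ(z)²/[p(1 − p)]. This is at most 0.637, reached when p = 0.5.

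| Assumed mean | z | Called low | Information kept |
|---|---|---|---|
| 90 | −0.375 | 35% | 0.60 |
| 100 | −0.875 | 19% | 0.48 |
| 110 | −1.375 | 8.5% | 0.31 |
| 130 | −2.375 | 0.9% | 0.07 |

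If scores centre near 90, the stated cut does about as well as any two-way split can. If they centre near 130, almost everyone is high and little information remains. The article does not show which case applies.

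**The case against.** The strongest reply is that the only strict contradiction is harmless. Nobody can score 1 to 32, so reading the low band as 33 to 82 changes no woman's category. A cut need not sit at the midpoint, which is itself no validated threshold. The instrument is taken from cited sources, so a basis for 82/83 may exist there. That it came from halving 165 is an inference, though the arithmetic fits. All of this stands. The criticism of the cut is therefore that the article gives no basis for it and that it coincides with a calculation on the wrong floor. It has not been shown that another cut is the right one.

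A second reply also stands. Data Analysis allows Mann-Whitney tests or cumulative odds ratios for Likert scales, so the comparison between arms may not rest on the split at all.

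Stronger readings are tempting, and the documents do not support them:

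- **That nearly every woman will be called high, so an effect of the messages would be almost undetectable.** This holds only if mean scores are well above 100. The article gives no scores, and with a mean of 90 about a third of women would be low.
- **That baseline scores go unused.** Table 1 collects them, and Data Analysis foresees multivariable analyses if the groups differ at baseline. An article may leave further covariate detail to the analysis plan.
- **That the trial's main mechanism or main result is compromised.** The Study Design section presents self-efficacy as one element of the Health Belief Model, alongside perceived benefits, barriers and threat. Exclusive breastfeeding and the listed secondary outcomes do not use this score.
- **That a woman answering 3 throughout (total 99) is misclassified.** She is exactly at the midpoint, and a split placed there could put her on either side. The firm case is 83 to 98.

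**Conclusion.** The point holds in limited form. It is certain, from the article's own figures, that the low band begins at an impossible score and that the cut is half the maximum, 16.5 points below the middle of the attainable range. The 16 totals from 83 to 98 are consequently labelled high although they lie below the midpoint, without a stated reason.

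The consequence is confined to analyses that use the high/low form: the effect of the messages on self-efficacy and its relation to breastfeeding duration. The loss there could be modest or severe. With SD 20 assumed, the low group ranges from about 35% of women (mean 90) to about 1% (mean 130), and the information kept falls from about 60% to about 7% of that in the total score. No single figure in that range can be defended from the article. If the arms are compared by a rank test on the total score, that comparison is untouched and only the categorised results are affected.

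**What to change.** - **Analysed form.** Make the total score (33 to 165) the form analysed at months 1, 3 and 5, and compare arms with adjustment for the baseline score. Use the total score when relating self-efficacy to duration.
- **Categories.** Keep a high/low split for description only. Restate low as starting at 33. Either give a source for 82/83 or reset the cut, for example to 33 to 99 against 100 to 165, which puts 67 and 66 attainable totals in the two bands. A midpoint cut is a convention and should be described as one.
- **Consistency.** Align Baseline Data Collection, the Table 1 label and Data Analysis, so that the reader knows which form is tested and which is only described.

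**Cost.** No new data are needed. The items were already collected, so the work is rewording and recoding. The real cost is timing: the article reports that follow-up is complete and analysis is under way, so the change has to be disclosed as made after data collection. Reporting the categories as stated in the article beside the total-score analysis would let readers see whether the choice affected the result.

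### The self-efficacy bands do not fit the stated score range: the low band starts at totals that cannot occur, and the unexplained 82/83 cut is half the maximum, not the midpoint

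*Protocol article*

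**What the plan says.** The Baseline Data Collection section describes the instrument: "With 5 levels of responses to 33 items", coded as "no confidence= 1, somewhat confident= 2, sometimes confident= 3, confident= 4, very confident= 5". The same sentence gives the range and the two bands: "total scores range from 33 to 165 and will be categorized as low self-efficacy (1 to 82) and high self-efficacy (83 to 165").

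Table 1 lists the instrument as "Breastfeeding self-efficacy scores (high/low") at baseline and at months 1, 3 and 5. Follow-Up Data Collection gives it two analytic uses: the relation between self-efficacy and breastfeeding duration, and "whether text messages improved breastfeeding self-efficacy".

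The Data Analysis section provides Mann-Whitney tests or cumulative odds ratios for Likert scales, and chi-square tests for proportions. It does not say which of these applies to self-efficacy.

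**The concern.** The stated range and the stated bands sit in one sentence and do not agree. The range allows for the minimum of 1 per item; the bands do not. A low band starting at 1, together with a cut at exactly half of 165, suggests that the threshold was taken from the maximum alone.

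The wrong lower bound is harmless in itself, since nobody can score 1 to 32. The position of the cut matters more. A woman who averages slightly below the middle response is classed as having high self-efficacy. If most women score well above the middle, both groups will be almost entirely high. The binary variable then has little room to show a gain from the messages or to separate women by breastfeeding duration.

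**Working it through.** **Inputs from the protocol article.** 33 items coded 1 to 5, range 33 to 165, low 1 to 82, high 83 to 165 (Baseline Data Collection); 353 women and 13% expected loss (Sample Size Determination); 1:1 allocation (Abstract).

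**Reproducing the stated range.** 33 × 1 = 33 and 33 × 5 = 165. This matches. There are 165 − 33 + 1 = 133 attainable totals. Coding the items 0 to 4 would give 0 to 132, which does not match.

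**Reproducing the stated cut.**
- Half the maximum: 165/2 = 82.5, which gives 82 | 83 exactly.
- Midpoint of 1 to 165: (1 + 165)/2 = 83, nearly the same split.
- Midpoint of the attainable range: (33 + 165)/2 = 99, which is also 33 × 3, the total of a woman who gives the middle answer to every item. This does not reproduce the stated cut.

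**What the bands do.**
- Unattainable totals in the low band: 1 to 32, so 32 values.
- Attainable totals: 50 low (33 to 82) and 83 high (83 to 165), that is 37.6% and 62.4% of 133.
- Distance from the midpoint: 99 − 82.5 = 16.5 points, or 16.5/132 = 12.5% of the range.
- Totals below the midpoint but labelled high: 83 to 98, 16 values. Mean item score runs from 83/33 = 2.52 to 98/33 = 2.97.

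**Illustration of consequence.** The article gives no score distribution, so everything here is assumed: normal totals, SD 20, a gain of 0.3 SD (6 points), two-sided 5% test. Per group, 353 × 0.87 / 2 = 153.6, taken as 153.

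For a cut c and control mean m, the share high is p₁ = Φ((m − c)/20) in the control group and p₂ = Φ((m + 6 − c)/20) in the intervention group. With p̄ the average of the two,

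power = Φ{[(p₂ − p₁) − 1.96 √(2p̄(1 − p̄)/153)] / √([p₁(1 − p₁) + p₂(1 − p₂)]/153)}.

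Example, m = 110 and c = 82.5: p₁ = Φ(1.375) = 0.915, p₂ = Φ(1.675) = 0.953, difference 0.0376. Power = Φ[(0.0376 − 1.96 × 0.0283)/0.0283] = Φ(−0.64) = 26%.

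| Assumed mean | Control share high, stated cut (82.5) | Control share high, midpoint split (99.5) | Power, stated cut | Power, midpoint split |
|---|---|---|---|---|
| 80 | 45% | 16% | 55% | 45% |
| 85 | 55% | 23% | 54% | 50% |
| 90 | 65% | 32% | 51% | 53% |
| 100 | 81% | 51% | 40% | 55% |
| 110 | 92% | 70% | 26% | 48% |
| 120 | 97% | 85% | 15% | 36% |
| 130 | 99% | 94% | 8% | 22% |

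The midpoint column uses low 33 to 99, high 100 to 165. The other midpoint split (cut at 98.5) changes its power by no more than about 1.5 percentage points.

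For a Mann-Whitney test on the totals, with asymptotic efficiency 3/π under normality: Φ(0.3 × √(153/2 × 3/π) − 1.96) = Φ(2.564 − 1.960) = Φ(0.604) = 73%, whatever the mean.

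**The case against.** Four points can be made for the plan.

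1. **The impossible scores change nothing.** Low 1 to 82 and low 33 to 82 classify every woman identically. This stands; on its own it is a wording error.

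2. **The cut is not shown to be wrong.** A reader might infer that the article intended a midpoint split and miscalculated it, so that 99 is the correct value and the cut is 16.5 points too low. The article does not say so. It states no principle for the cut, and the instruments that it cites for the scale are not available here. The figure of 165/2 is inferred from the numbers. The inference is reasonable, because no other reason is given and the low band ignores the minimum in the same way, but it remains an inference.

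3. **A ceiling is not demonstrated.** A reader might also conclude that nearly every woman will be classed as high and that the reported share will be overstated. Without a score distribution, neither can be established. The number of women scoring 83 to 98 is unknown. The power comparison also reverses at low means: at 85 the stated cut gives 54% against 50%, and at 80 it gives 55% against 45%. This stands, so the loss of power can only be stated conditionally.

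4. **The analysis may not use the cut.** The article calls self-efficacy a Likert scale, and Data Analysis allows rank-based or cumulative-odds methods for such scales. This stands in part. Table 1 labels the variable high/low and the bands are written as a rule that will be applied, so a chi-square test on the binary variable is equally open.

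**Conclusion.** The article contradicts itself on the attainable range, and it applies a cut that is half the maximum without giving a reason. Both follow from a single sentence and need no assumption. It also follows that 16 totals below the middle of the scale are called high.

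The effect on results is conditional. If scores sit well above the midpoint (assumed mean 110 to 120, SD 20), the stated dichotomy has 15% to 26% power for a 0.3 SD gain, against 36% to 48% for a midpoint split. If the mean is about 85 or lower, the stated cut is no worse than the midpoint. In every scenario tabulated, either dichotomy does worse than the total score at about 73%. Replacing one cut with another is therefore the smaller part of the remedy.

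Severity is minor to moderate. Self-efficacy is not among the primary or secondary outcomes in the Outcome Measures section, and neither the sample size nor the main conclusion depends on it. It does bear on two questions that the article says it will answer, and on a component of the trial's Health Belief Model.

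**What to change.** 1. Start the low band at 33.
2. Use the total score for the comparison between groups, with the Mann-Whitney test that Data Analysis already allows, and enter the total score, not the high/low variable, in the analysis of breastfeeding duration.
3. Keep high/low for description only. Place the cut at the midpoint of the attainable range (low 33 to 98 and high 99 to 165, or low 33 to 99 and high 100 to 165) unless a source for 82/83 is cited. The two midpoint splits differ only in where a total of 99 falls; choose one and state it.
4. Follow-up was complete and analysis under way when the article was written. Record the change and its reason, and fix it before self-efficacy is compared by group or related to duration.

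The cost is a line or two of text and a recode of stored totals at baseline and months 1, 3 and 5. The reported share with high self-efficacy may be lower than under the present bands.

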### Follow-Up Data Collection

Follow-up comprised a postdelivery survey, feeding follow-up assessments, morbidity, breastfeeding self-efficacy, and social desirability assessments. Questionnaires have been adopted from the Global Strategy for Infant and Young Child Feeding [6] indicators for assessing infant and young child feeding recommendations by WHO [38-40], breastfeeding efficacy scales [41,42], a short version of the Marlowe-Crowne Social Desirability Scale [43], and unpublished questionnaires being used in ongoing projects in Bangladesh (MJD and ML) and Indonesia (MJD).

The postdelivery form was completed when the child was 10 days old and was used to assess his or her postdelivery status, including the date, place, and type of delivery and the child’s birth weight, sex, and perinatal outcomes. The feeding follow-up form was completed every month and asked if the child was breastfed and if other liquids or foods were given in the last 24 hours and over the preceding month since the last contact (or birth for the first follow-up). Each participant completed 6 assessments of their feeding practices, including detailed information about the different types of liquids and foods (Textbox 1).

Child morbidity status and self-efficacy were assessed when the child was 1, 3, and 5 months of age using items from a validated instrument [7,41,42]. Child morbidity questions were used to record whether the child has had any signs or symptoms such as fever, cough, cold, running nose, rapid breathing, difficulty in breathing, chest indrawing, and diarrhea and dysentery. If one of these was present, we further explored the duration of illness. Breastfeeding self-efficacy was collected at 1, 3, and 5 months postdelivery to ascertain the mothers’ confidence to breastfeed, the relationship between self-efficacy and breastfeeding duration, and whether text messages improved breastfeeding self-efficacy. Studies report that women with a higher perceived self-efficacy for breastfeeding tend to initiate breastfeeding and persist even through challenges, and we hope that women in our study will increase their confidence or self-efficacy to continue EBF because of the knowledge gained from the text messages they received [41,42,44,45].

List of different types of liquids and foods.Liquids or fluids:Plain waterJuice or juice drinks, honeyOralit or any oral replacement therapy (ORS), including fruity ORS made in ChinaVitamin drops or other medicines as drops including traditional Burmese medicineInfant formula milk such as Nestle, Dumex, Chinese brands^a^, and Red CowMilk that is tinned or powdered (PEP, Red Cow) or fresh animal milk such as cow or goat milkClear broth or other soup, such as chicken, beef, or fish brothAny other water-based liquids such as sugar water, rice water, green tea, tea, coffee mix, or sodaSoya milk or yogurtSemisolid and solid foods:Branded baby food, such as SUN, Nestle, Dumex, Chinese brands^a^)Rice powder, cooked or blended rice, bread, noodles, porridge, or other foods made from grains such as sagoPumpkin, carrots, squash, or sweet potatoes that are yellow or orange insideWhite potatoes, yams, manioc, cassava, or any other foods made from rootsAny dark green leafy vegetables such as water cress, drum stick, lady finger, and spinachFruit rich in vitamin A such as ripe mango, papaya, jack fruit, oranges, and persimmonsAny other fruits or vegetables such as banana, guava, apples, green beans, and peasLiver, kidney, heart, or other organ meatsAny meat such as beef, pork, lamb, goat, chicken, or duckEggsFresh or dried fish, dried shrimp, or other seafood^a^Chinese brand milk products means imported milk products from the Myanmar-China border with or without registration.

We also assessed social desirability status, which is the tendency respondents have to answer questions in a way that is viewed favorably by others (such as research team members). This can interfere with the interpretation of average tendencies as well as individual differences [43]. By measuring social desirability status, we were able to assess whether follow-up data were influenced by bias. We used the validated and reliable short version of the Marlowe-Crowne Social Desirability Scale, which is based on a subset of 13 items adapted from Reynolds and Gerbasi [43].

